### Evaluation of cost:

We will compare the medical and non-medical costs between the two groups of patient. Costs will be identified for a one-year time. .

For this purpose, resource use in each arm will be collected in physical units in the eCRF at each clinical centre as follows:

- Acute care medical hospitalisations related to IDD
- Acute care surgical hospitalisations related to IDD
- Rehabilitation hospitalisations related to IDD
- Analgesics
- Work disruption

### Safety Outcomes

Prior to enrolment into the trial, subjects will undergo a thorough screening to assess their eligibility for the study, including X-ray and MRI of the lumbar spine, recording of medical history, concomitant medications, vital signs, physical examination, pregnancy test, routine laboratory testing, urinalysis and serological test of infections.

The results from the above mentioned examinations and tests will be used as baseline values and comparators, if and as far as changes of these parameters will occur during the trial.

During each visit to the study centre, participants will undergo a physical examination with recording of vital signs, blood sampling for assessment of routine lab tests, urinalysis, a spine examination and an assessment of pain. Furthermore, if the study patients do not spontaneously report any AE occurrence since their last

visit, they will be interviewed by the investigator filling a study-specific AE checklist for recording of symptoms and complaints.

If an AE occurs at a moment in-between two study centre visits and participants feel that they should consult a physician, they have to call or visit the emergency service of reanimation referring to their participation in the study.

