## 1.4 Risks

A large number of trials have risen rapidly investigating the efficacy in treating conditions such as type I and II diabetes, liver cirrhosis and regeneration, fistulas, cardiovascular disease (ClinicalTrials.gov Identifier NCT00999115), limb ischemia, amyotrophic lateral sclerosis and lipodystrophy (<http://clinicaltrials.gov>). More than 400 trials have been conducted with more than 1000 patients treated with MSC. Furthermore, BM-MSC are also under examination in clinical case studies for graft-versus-host disease immunosuppression, rheumatoid arthritis, Crohn's disease and ulcerous colitis, multiple sclerosis, soft tissue augmentation and bone tissue repair (Fang et al., 2006; Fang et al., 2007) with a clinical benefit, as well as appropriated tolerance. Clinical experience is available with both autologous and allogeneic BM-MSC administration.

- Systemic effects: The autologous nature of the study medication effectively excludes the risks of transmission of infectious agents, graft rejection, or GVHD (Graft versus host disease). The risk of systemic infection, bacteraemia, or sepsis due to contamination of the cell preparation is negligible. .
- Local effects: the complications are the same as in the discography, and rarely presented. The most common complaint is the exacerbation of pain for 1-2 weeks, which is usually solved by analgesia and muscle relaxants for a short period. The most serious complication is discitis, occurring in less than 0.1 % (Osti et al., 1990). Procedure related adverse events such as of infections, bleedings, nerve irritations and nerve injuries with its possible consequences paresthesia and paralysis are exceptional during the injection using the CT scan or fluoroscopic guidance, but patients will be informed.

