#### **6.2.6 Visit 1: Month 1**

- Vital signs
- Physical exploration
- Blood sampling for routine laboratory testing
- Urinalysis
- Pain assessment of the lumbar spine by visual pain scale (VAS)
- Oswestry Disability Index in order to measure a patient's permanent functional disability, Quality of life assessment using SF-36
- Adverse event assessment
- Instruction for wash out (NSAIDS washout of at least 2 days before this Visit, no painkillers 24h before the visit)
- Prohibition of NSAIDs
- Concomitant medication

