### **6.3 Unscheduled visits**

If subject gets in contact with the site between regular visits due to acute disorders, an unscheduled visit will promptly be performed at the site. During this additional visit a physical examination, a systematic interview for recording AEs should be performed. In case of suspected local infection (nocturn lumbar pain, temperature above 38°C), disc puncture will be performed and an empirical antibiotic treatment will be initiated immediately and further tuned according to the antibiogram

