### **7.3 Safety analysis**

Adverse events that occur during this study will be presented by system organ class (SOC), high level term (HLT), and preferred term (PT) in a frequency table giving the number of events, the number of subjects, and the percentage of subjects who experience the event by treatment group.

Subjects with multiple AEs will be counted only once within each PT, HLT, and SOC.

Coding of the AEs will be performed with the Medical Dictionary for Regulatory Activities.

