#### **8.5 Investigator responsibilities**

##### AEs

Complete and appropriate data on all AEs (only clinically significant event or value) experienced during the clinical trial should be recorded on the AE form of the CRF on an ongoing basis for the duration of the study. Each AE report shall include a description of the event, an assessment of its seriousness according to the criteria listed above, its duration, intensity, relationship to the study medication, other causality factors (if any), any concomitant medication dispensed, actions taken with the study drug or other therapeutic interventions and outcome at the end of the observation period.

The adverse events will be encoded and graded according to CTCAE Criteria Grade 1-5

(Common Terminology Criteria for Adverse Events). A copy of the CTCAE Version 5.0 can be downloaded from the CTEP homepage (<http://ctep.info.nih.gov>). If there is no CTCAE grading possible, the intensity of the adverse event has to be classified in categories:

- Mild (Grade 1) – transient or minimal symptoms; no change in activity or need of medication
- Moderate (Grade 2) – symptomatic; moderate change in activity; no reduction in social activities

- Severe (Grade 3) – incapacitating; bed rest required; loss of work; reduction in social activities
- Life threatening (Grade 4) – significant clinical intervention or hospitalization required
- Fatal (Grade 5)

For each AE, a separate AE form will be filled in.

Follow up of AEs: AEs will be followed until their resolution or stabilisation. However, the observation period will be cut off after the last patient has finished his final visit (LPLV). During monitoring visits, the study monitor will assess accuracy and completeness of all AE forms generated since the last visit by 100% source data verification. Cases of AEs reported earlier for which the outcome is still pending will be checked for new data and developments. Furthermore, queries on AEs reported earlier will be solved with the Investigator. AEs will be reported in the final study report.

The sponsor must be informed immediately of the occurrence of any AE grade 3-4-5 by the associated centre.

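### At scheduled visits the AE checklist goes only to patients who volunteer no event, so additional events are under-recorded and the per-term AE tables may be biased if volunteering differs by arm

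*Protocol*

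**What the plan says.** The rule for scheduled visits is one sentence under Safety Outcomes in Section 4.2. It applies "if the study patients do not spontaneously report any AE occurrence since their last" visit; in that case, at the "visit, they will be interviewed by the investigator filling a study-specific AE checklist for recording of symptoms and complaints". Patients who do report something are not mentioned.

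Other parts of the Protocol bear on how AEs are found:

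- Sections 6.2.5 to 6.2.10 list "Adverse event assessment" at baseline and at months 1, 3, 6, 12 and 24, without a method.
- Section 6.3 (Unscheduled visits) says that "a systematic interview for recording AEs should be performed", with no condition attached.
- Section 8.5 sets a recording duty: "Complete and appropriate data on all AEs (only clinically significant event or value) experienced during the clinical trial should be recorded". It does not say how events are to be elicited.

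On use of the data, Section 7.3 tabulates AEs by system organ class, high level term and preferred term, giving events, subjects and percentages for each arm. Section 8 names the type of event and its distribution between arms as a measure of safety. Section 2.4.2 uses the number of participants with AEs, their relation to the product and their severity.

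**The concern.** Whether a patient is actively questioned at a scheduled visit depends on what that patient has just volunteered, which is itself a post-randomisation outcome. Solicited and unsolicited reporting are mixed in proportions that can vary by arm. Symptoms a patient does not think to mention are the ones a checklist is meant to find, and they are missed whenever something else was mentioned first. No later analysis can recover a symptom that nobody asked about.

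There is a reason why volunteering might differ. Section 1.4 says of disc injection: "The most common complaint is the exacerbation of pain for 1-2 weeks". Under Section 5.6 sham patients have a muscle puncture and no disc injection, and under Section 5.2 the sham needle does not enter the iliac crest. If more cell-arm patients come to month 1 reporting a pain flare, more of them skip the checklist at the visit best placed to pick up the other reactions expected in Section 8.3, such as raised temperature, shivering, pruritus, headache and nausea. Those terms would then look rarer with cells than they are.

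**Working it through.** The plan states no figure on this point, so there is none to reproduce. The size is explored with a small model whose inputs are **all assumptions**, except the 26 patients per arm (Section 2.1).

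**Model.** For one visit interval and a second event B with the same true risk in both arms:

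- b = true risk of B, set at 0.20
- v = chance that a patient with B volunteers it, 0.2 or 0.4
- s = chance that the patient volunteers some other event, which switches the checklist off
- c = chance that the checklist finds B, set at 0.9

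Recorded under the Section 4.2 rule: b × [v + (1 − v) × (1 − s) × c].

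Recorded with the checklist for everyone: b × [v + (1 − v) × c], which does not contain s.

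**Worked case**, v = 0.2, cell s = 0.60, sham s = 0.20:

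- Cell: 0.20 × [0.2 + 0.8 × 0.4 × 0.9] = 0.20 × 0.488 = 0.098, about 2.5 of 26
- Sham: 0.20 × [0.2 + 0.8 × 0.8 × 0.9] = 0.20 × 0.776 = 0.155, about 4.0 of 26
- Ratio: 0.098 / 0.155 = 0.63
- Checklist for everyone: 0.20 × [0.2 + 0.8 × 0.9] = 0.184, about 4.8 of 26 in each arm

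**Range of the recorded cell-to-sham ratio:**

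| s, cell v sham | v = 0.2 | v = 0.4 |
|---|---|---|
| 0.20 v 0.20 | 1.00 | 1.00 |
| 0.30 v 0.20 | 0.91 | 0.94 |
| 0.40 v 0.20 | 0.81 | 0.87 |
| 0.60 v 0.20 | 0.63 | 0.74 |

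In the first row both arms still lose events: 0.155 recorded against 0.184 at v = 0.2, and 0.166 against 0.188 at v = 0.4. The rule alone under-records. It distorts the comparison only when s differs. If sham patients volunteer more, the ratios invert: the 0.81 to 0.87 row becomes 1/0.87 = 1.15 to 1/0.81 = 1.23.

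**Any-AE count.** Let q be the chance of an event that only the checklist would find. Under the rule, a patient has at least one recorded AE with probability s + (1 − s)q. With the checklist for everyone it is 1 − (1 − s)(1 − q), which is the same expression. With s = 0.60 and q = 0.30 both give 0.72; with s = 0.20 both give 0.44. A patient who skips the checklist already has a reported event, so this count does not change.

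**The case against.** The strongest reply is that the sentence does not say that a patient who reports an event is asked nothing more. An AE assessment is listed for everyone at each visit, Section 8.5 asks for complete data, and every visit includes examination, laboratory tests and a pain assessment. Section 4.2 also has a diary of painkiller use with indication, checked at each visit. These routes will catch some second events. None of them is a uniform set of questions, so the gap remains for symptoms that leave no trace in an examination or a diary.

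Three stronger readings are tempting and are not supported.

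- *Such a patient is never systematically asked.* The condition is reset at each visit, and Section 6.3 adds a systematic interview at unscheduled visits. What is lost is the interval in question. A later checklist need not reach back to it, and the last interval, from month 12 to month 24, is long.
- *The tables are biased in favour of the cells.* This needs unequal volunteering. Section 1.3 reports no significant difference in mild reactions between sham and treated patients, although the two studies cited just before that statement are listed in Section 17 as knee osteoarthritis studies. Sham patients also have needle punctures, and patient and assessor are blinded (Section 3.3). The pain flare lasts 1–2 weeks, so it bears mainly on month 1. Later the direction could reverse: Section 7 expects 68% responders with cells against 30% in controls, and Section 8.2 counts deterioration of existing disease as an AE, so sham patients might volunteer more.
- *The rule halves the recorded rate with cells.* A ratio of (1 − 0.60)/(1 − 0.20) = 0.50 arises only at 60% against 20% volunteering and if second events are never volunteered. Once some are, the same pair gives 0.63 to 0.74.

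It can also be said that Sections 4.2 and 6.3 do not contradict each other, since one covers routine visits and the other acute ones. That is right. Section 6.3 shows only that an unconditional interview is already accepted elsewhere in the Protocol.

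**Conclusion.** The point stands in a limited form. As written, Section 4.2 makes the checklist at scheduled visits conditional on silence, and no other section gives it to every patient there. Additional events are under-recorded in both arms. Event counts and per-term tables may be distorted between arms if spontaneous reporting differs, which is plausible around month 1, not established, and of uncertain direction afterwards.

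Under the assumed inputs, the recorded ratio for an equally frequent second event runs from about 0.63 to 0.94 for 30% to 60% against 20% volunteering, and is 1.00 if volunteering is equal. These ratios illustrate sensitivity; they do not predict what this trial will show. The number of participants with any AE is not affected, and the Section 7.3 table is descriptive, so the consequence is confined to the safety profile by term and by number of events. The correction is cheap and worth making.

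**What to change.** Replace the conditional sentence under Safety Outcomes in Section 4.2 with a rule of this kind: at every scheduled visit, every patient is first asked an open question about events since the last visit and is then taken through the same study-specific AE checklist, whatever was volunteered. Add a field to the AE form that marks each event as spontaneous or solicited, and have Section 7.3 tabulate both by arm.

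This removes the dependence on volunteering: in the model above the ratio becomes 1.00 whatever the difference in s. The checklist already exists. The cost is a protocol wording change, one extra field and a few minutes per visit. The downside is that more mild events will be recorded, which the spontaneous or solicited flag helps a reader to interpret.

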## **5. Presentation of the Investigational Medicinal Product**

### **5.1 Obtaining, purifying and expanding MSC.**

MSC will be obtained following GMP-compliant internal procedure: autologous BM will be seeded w/o any additional manipulation in semi-closed cell culture system (CellSTACK, Macopharma) in Alpha-MEM+10% EDQM certified fetal bovine serum (FBS). MSC will be obtained within 72 hours by plastic adherence; after removal of non-adherent cells, medium will be changed twice a week, w/o neither differentiation nor commitment of cells. Trypsinization will be performed at day 14 and 21 (+/-1 days) using GMP qualified reagents. The final product will undergo to the follow quality controls: Cell count, Immunophenotype, Viability, Endotoxin test (Ph. Eur. 2.6.14), Sterility test (Ph. Eur. 2.6.27), Mycoplasma (Ph. Eur. 2.6.7), karyotype. Aliquots are cryopreserved for additional testing if necessary.

### **5.2 Methodology for obtaining bone marrow autologous**

Patient positioning: the patient is in prone position. Bone marrow (BM) is harvested from the posterior superior iliac crest region. Monitored anesthesia (conscious sedation) and local anesthesia will be used. After palpation of the bony landmarks, the procedural site is sterilely prepared and widely draped to ensure an adequate field.

Bone Marrow Aspiration: A Jamshidi needle is used. The skin is then injected down to and including the periosteum with 1% lidocaine without epinephrine. Then, the bone marrow aspiration trochar and needle are percutaneously inserted through the skin and subcutaneous tissues until it reaches the posterior iliac crest. Then, manual pressure is used to position the bone marrow aspiration trochar against the dense cortical bone, centering it over the middle of the posterior crest cortical walls. After the trochar is inserted into the posterior iliac crest but prior to aspiration, 1 mL of heparin (1,000 U/mL) will be preloaded into the syringe. Approximately 20 mL of bone marrow is aspirated, by using two 20-mL syringes. At conclusion a sterile dressing is applied.

The transport container with the raw material, is delivered to the manufacturer. Upon arrival, the container is inspected and the specimen is taken out to the clean-room

for processing. The duration of transport and temperature is recorded. Coherence with accompanying documents is controlled, including donor identifiers.

The sham procedure will consist of the same setting and instruments. The Jamshidi needle will be percutaneously inserted through the skin and subcutaneous tissues and not inserted in the posterior crest .

### **5.3 Packaging and conditioning for shipping of final product.**

The CF-BM-MSD will be prepared in 3 Luer-lock syringes, each containing 2 mL of cell suspension (normal saline solution (0.9% NaCl)+ human albumin 5%) at a cell concentration:

( $45 \pm 3 \times 10^6$  total MSD)

Cell concentration:  $7.5 \times 10^6$  cells/mL

That is:  $15 \pm 1 \times 10^6$  cells per syringe in 2 mL

Number of syringes: 3 Total volume: 6 mL

### **5.4 IMP labelling, storage and handling**

The IMP is labeled by the manufacturer according to the applicable regulatory requirements ensuring the traceability and attribution to the individual recipient of the autologous IMP.

The manufacturer ensures a continuous transport of the IMP with the accompanying documents in compliance with the regulatory requirements. A specialized transporter accordingly instructed by the manufacturer delivers the respective IMP to the clinical trial site.

The transport will be done between 4 and 8 °C, with temperature traceability. A suitable mode of transportation ensures delivery of the product to administration site.

### **5.5 Application of the cells**

Material Preparation: Cells tend to aggregate during transport, therefore, prior to application, this effect will be compensated by subjecting the syringe to a gentle oscillating movement allowing the cells to resuspend.

Patient Preparation: It will be verified that the informed consent document, the preoperative tests, and the medical history (that may be of interest during the procedure) are available. An antibiotic prophylaxis will be performed. The prophylaxis is the following: 2g Cefazolin, 1/2 hour before injection. Or in case of allergy: Clindamycin 900 mg (1/2 h before injection). The antibiotic solution is to be delivered intravenously (IV).

**Patient positioning:** The patient will be placed on a radiolucent surgical table and Wilson frame in a lying prone position. Once the patient is installed, the C-arm mobile radioscopy system will be positioned and tested and the skin prepped.

**Intradiscal cellular injection procedure:** The injection will be done by fluoroscopy. The investigator enters the images amplifier in the field. The adequate point of entry into the disc will be assessed by fluoroscopy and marked on the skin. The local anaesthesia will be infiltrated. The tip of the needle will advance until it punctures the disc and penetrates the nucleus pulposus. Controls will be carried out in anteroposterior and lateral planes to check the correct position of the needle, prior to the infusion of the cell suspension. After removing the needle mandrel, the syringe will be screwed to the needle and the cellular suspension (2ml containing  $15 \pm 1 \times 10^6$  MSC) will be slowly injected, stopping temporarily if the pain is exacerbated. A small Mepore dressing will be put into place.

### **5.6 Application of sham procedure**

In the other group, the sham procedure will be performed in the same conditions in order to keep blind the patient. The person in charge of injection, who's the only unblinded investigator will mimic intradiscal injection by using imaging with only paravertebral muscle puncture. No disc injection, no placebo injection will be performed in the control patients.

The annulus will not be perforated. A puncture with a needle into deep muscle (Musculus erector spinae) will be performed, however no lidocaine or other fluids will be delivered in the vicinity of the disk, as to avoid any positive or negative bias. As the patient will be lying on the table and covered by the drape, he/she will not be aware that the C-arm is not in action during the procedure.

### **5.7 Post-treatment care**

The patient is discharged after an observation period of 2 hours. Walk for moderate periods is authorized. Labor activity is suspended for one week. The pain medication is tailored to the needs of each patient and the use of NSAIDs should be avoided. The longterm monitoring will consist of out-patient visits and MRI.

The patients are followed for 2 years on clinical examination, spine MRI. For 2 years they will be followed annually on clinical basis to assess any unexpected long term side effect.

In case the patient have not responded after end of study (3 years) or relapse, he may be eligible for cell therapy when the product will be available on routine basis, or benefit for treatment recommended by EULAR (physiotherapy, steroid or surgery)

### **5.8 Possible complications of this therapy.**

The complications are the same as in the discography, and rarely presented. The most common complaint is the exacerbation of pain for 1-2 weeks, which is usually solved by analgesia and muscle relaxants for a short period. The most serious complication is discitis, occurring in less than 0.1 % (Osti et al., 1990). Other complications described, although much less frequently, are transient headache, nausea, meningitis, epidural abscess, arachnoiditis, intrathecal hematoma, retroperitoneal hematoma, cauda equina syndrome and acute disc herniation. Cases of urticaria are not likely in this therapy, as they are attributable to the radiologic contrast, which is not used here. Initial fears about the possible long term side effects of discography regarding the disc viability have not been confirmed. A 20-year of clinical follow-up did not find radiographic evidence of progressive disc degeneration after the discographies (Flanagan & Chung , 1986).

There is no risk of rejection using autologous cells.

